## Abstract

**Background:**

Gross motor function impairments and manual dexterity deficits are frequently observed in children and adolescents with Cerebral Palsy (CP), having a major impact on their activity level and autonomy. Improving manual dexterity and activity level of patients with CP is often the focus of rehabilitation. Novel and adjuvant treatment methods that could support the standard training also in chronic conditions are a research priority. The transcutaneous Vagus Nerve Stimulation (tVNS) is a non-invasive brain stimulation technique, which provides a bottom-up stimulation of subcortical and cortical brain structures, enhancing brain GABA and Noradrenaline levels. This technique may play a pivotal role in brain plasticity, which has not been tested in CP patients before.

**Methods:**

44 children and adolescents with CP will be involved, treated in pairs in a randomized, double-blind, pre-post test study. The two groups will undergo the Hand-Arm Bimanual Intensive Therapy Including Lower Extremities (HABIT-ILE) for 2 consecutive weeks, with 3 h daily sessions for 5 days per week, for an overall time interval of 30 h; the training will be combined with the application for 75 min/day of active or sham tVNS, in separate, randomly allocated groups. The primary outcome measure will include the scores at the Assisting Hand Assessment and Box and Block Test, and at an *ad-hoc* visuomotor task evaluating manual visuomotor control. Secondary outcomes will include the scores at the Children’s Hand Experience Questionnaire, Canadian Occupational Performance Measure, Melbourne Assessment of Unilateral Upper Limb Function, Gross Motor Function Measure, Vineland, Pediatric quality of life inventory. The evaluation points will include pre (T0), post (T1) and 3-month follow up (T2) assessments. Safety and tolerability will also be assessed.

**Results:**

The results of this trial will assess whether tVNS can effectively boost the effects of an intensive two-week bimanual training, in improving manual dexterity in children and adolescents with cerebral palsy, ensuring safety and tolerability throughout the intervention period.

**Clinical trial registration**:  ClinicalTrials.gov, NCT06372028.

## Highlights

Enhancement of the effectiveness of intensive bimanual training.Set of best practice parameters of tVNS in pediatric patients.Proof of safety and tolerability of tVNS in the CP population.

## Introduction

Intrauterine or neonatal encephalopathy, whether vascular, infectious, or neuroinflammatory in origin, is a cause of brain destruction and reorganization and can lead to serious, debilitating conditions, including neurodevelopmental impairments such as Cerebral Palsy (CP) (1). The term of CP describes a group of permanent disorders compromising movement and posture, causing activity limitation, often accompanied by disturbances of sensation, perception, cognition, communication, and behavior. These difficulties directly impact social participation and quality of life of children and their families until adulthood (2, 3), with an overall prevalence of 2.11 per 1,000 live births (4, 5).

Depending on brain lesion location, either bilateral or unilateral CP may be observed. Upper limb functionality has a huge impact on a child’s ability to carry out self-care tasks and participate in leisure and learning activities. Indeed, patients often experience frustration when attempting to perform everyday two-handed tasks, and they display greater negative reactions to failure than their typically developing peers (6).

While there is no cure, there is a wide consensus in the literature on the importance of an early and intensive intervention to alleviate negative impact. Many different approaches based either on the training of a motor ability or the training of a task to achieve a goal or to acquire motor skills have been proposed and systematically compared (3, 7, 8). It emerged that interventions based on the repetition of isolated movements are less effective compared to interventions aimed at achieving a goal and acquiring skills that can become an integral part of a child’s daily routine (9). In these more effective interventions, the child is actively engaged in practicing age-appropriate tasks and movements that are relevant for him/her (7, 8, 10, 11). Of note, age plays an important role, since children under 8 years of age were more likely to succeed in improving their motor ability (3).

In the last decade, several task-specific interventions have been shown to be effective in children with unilateral CP. Among these, the bimanual therapy involved in the Hand-Arm Bimanual Intensive Therapy (Habit) has gained growing interest. It is an intervention where use of both hands in cooperation is required, aiming to increase functional independence during daily living. Starting from the HABIT, the HABIT Including Lower Extremities (HABIT-ILE) has been proposed as a form of bimanual training continuously incorporating also postural control and Lower Extremities function and tested in a randomized controlled trial in children with unilateral CP (12, 13). While both HABIT and HABIT-ILE were shown to be effective in improving Upper Extremities functions, interestingly, with respect to the HABIT, the HABIT-ILE induced larger functional improvements in activities of daily living involving the Lower Extremities (14).

Despite the possibility to improve upper extremities functions and daily living through these intensive trainings, there is a need to identify new forms of intervention that act more directly on brain plasticity to optimize neurorehabilitation effects especially in older children. This is particularly important when considering the cases in which the programs for improving fine and gross motor functions are delayed to a later, more chronic stage, with respect to the cerebral perinatal insult, due to the need of dealing with oral motor disorders or to other life-threatening conditions in the acute phase. Moreover, as the children grow, and brain plasticity slightly decreases, the needs and the desired goal of the individuals change, making it important to find a way to boost brain plasticity in combination with individualized rehabilitation training.

In this vein, vagus nerve stimulation (VNS) has been held as a tool to enhance the effect of motor rehabilitation in neurological disease like stroke (15). Animal models have demonstrated that pairing VNS with motor experience can result in cortical reorganization that can provide beneficial effects in stroke by driving specific forms of cortical plasticity (16). In rodent models of ischemic stroke, VNS combined with movement training significantly improved forelimb motor recovery and tripled the synaptic connectivity of motor cortex neurons compared with movement training alone. Interestingly, these benefits were stable after 6 weeks and the VNS-dependent recovery generalized also to similar untrained movements (17). In humans, the effects have been tested by Dawson et al. (18), who evaluated the clinical changes induced by VNS paired with physical rehabilitation in a pilot study with stroke patients. In this study, VNS was paired with several typical rehabilitative tasks over the course of 6 weeks of physical rehabilitation. At the conclusion of therapy, patients who received active VNS paired with rehabilitation demonstrated a significant increase of Upper Extremity Fugl–Meyer score compared with patients who received the same rehabilitation with sham VNS. The improved forelimb function persisted when evaluated 30 days after the conclusion of therapy, potentially suggesting a long-lasting recovery of function. In summary, researchers demonstrated a stronger enhancement in motor functions when motor rehabilitation was paired with VNS compared to when paired with sham VNS, in post-stroke patients. Unfortunately, VNS necessitates a costly, invasive surgical procedure.

In the last years, transcutaneous VNS (tVNS) has been proposed as a noninvasive and patient friendly method to stimulate the vagus nerve, through the skin, by delivering weak electric current to the sensory afferent fibers of the auricular, thick-myelinated, branch of the vagus nerve in the outer ear (19). Such stimulation activates the auricular branch of the vagus nerve and, via this pathway, the nuclei of the nerve located in the brainstem, enhancing brain GABA (20) and Noradrenaline (21) levels, which plays a pivotal role in brain plasticity (22). Since neuroimaging (23) and neurophysiological (20) studies suggested that the effect of tVNS on brain activity is quite similar to the effect induced by traditional, invasive VNS, tVNS has been proposed for the treatment of different clinical conditions including that consequent to stroke (24–30).

Considering the effectiveness of VNS in improving motor function following stroke in adults (18), the present study aims to investigate the effects of tVNS in the pediatric population with CP. The application of non-invasive brain stimulation (NIBS) techniques, such as tVNS, is encouraged also in pediatric populations (31, 32), with prior research indicating that NIBS modalities are generally safe and well tolerated also in children with brain injury (33–35).

With the present trial, we aimed at testing the boosting effects of tVNS when paired with an intensive bimanual training on motor functions in children and adolescents with CP.

Two groups of patients will receive active or sham tVNS paired with the HABIT-ILE protocol. In both groups, the intensive bimanual training will aim to the achievement of the goals that the children and their parents choose themselves, therefore tailored to patients’ needs and highly motivating.

We hypothesize, for both groups, an improvement after the training in the clinical assessments of hand motor ability and daily functioning. However, we also expect that patients treated with HABIT-ILE Training paired with active tVNS will show a greater and more lasting improvement compared to the patients receiving the HABIT-ILE protocol paired with sham tVNS (36). Furthermore, we anticipate that patients will not experience major adverse events due to tVNS (34).

## Design

This clinical trial represents one of the two Randomized Clinical Trials (RCT) of the project “Bottom-up and tOp-down neuromOdulation of motor plaSTicity in cerebral palsy” (BOOST; FRRB 3438840). The study is a randomized, double-blind, sham-controlled pre-post-test study involving 44 children and adolescents with CP. Patients will be treated in pairs, with a matching of motor deficit severity, IQ, or age, by meeting at least two out of these three criteria. Motor severity will be defined on the basis of the Manual Ability Classification System (MACS) level and classified as low to middle (I-II level) or as middle to high (II-III). With respect to age, two group levels will be identified for children (from 6 to 11 years old patients) and adolescents (12–17 years old patients). With respect to IQ, low IQ value (from 50 to 70) and high IQ value (> 71) will be distinguished. Each pair will be randomly assigned to the active or to the sham tVNS group. The randomization will be stratified based on IQ, MACS level, or age. As for the matching within each pair, at least two out of these three criteria must be encountered.

Both groups will undergo a bimanual training in an ecological and highly motivating environment while carrying out bimanual tasks, including recreational play activities during the application of the tVNS protocol. During the training, starting from a set of proposals the choice of the type of activities to be practiced in each session will be left to patients, boosting the motivational aspect of the training. This will also ensure an individualized and goal-directed approach. The therapists will monitor and modify the activities within each pair to ensure that the intervention maintains the quality of the individualized intervention. The positions performed during bimanual tasks and the activities of daily living will be designed to systematically engage postural control of the trunk and lower limbs according to Habit-ILE protocol. The training will be carried out by a therapist with expertise in maintaining the 1:2 ratios. Training activities will be carried out for 5 consecutive days for 3 h/day for 2 weeks (30 h of intervention overall). Children and adolescents will be assessed 1 or 2 days before the start of the treatment (T0), 1 or 2 days after the end of the treatment (T1), and at a follow-up after 3 months (T2).

The overall RCT will be structured as follows. In the first session, prior to the beginning of the training (T0), the RCT will include the administration of all clinical assessment measures and the patients will be asked to perform for 10 min an *ad-hoc* computer based Visuomotor task (please refer to the outcome sessions for more a detailed description). Then, patients will undergo the 10-day treatment. For each training day, the treatment will last 3 h. During the first 75 min of treatment, the active or sham tVNS (according to group allocation) will be delivered. Before starting, 20 min after and soon after the end of the stimulation, the vital parameters will be checked. After the end of the stimulation, patients will be also asked to rate the sensations experienced during the stimulation through Visual Analog Scales and through child-friendly Likert scales. Then, they will continue the training for the remaining session time without stimulation. Soon after the end of all the training sessions, patients will carry the T1 evaluation. As for the T0 session, this session will include the administration of the clinical assessment measures and the execution for 10 min of the Visuomotor task. Three months after the end of the training (T2), the follow up assessment will be conducted, following the same exact procedure of T0.

Primary outcomes will include the following clinical measures: Assisting Hand Assessment (AHA), Box and Block Test (BBT), and performance at the Visuomotor task. Secondary outcomes will include the scores at the following tests: Children’s Hand Experience Questionnaire (CHEQ), Canadian Occupational Performance Measure (COPM), Gross Motor Function Measure (GMFM-66); Melbourne Assessment-2 (MA2) scale, Vineland Adaptive Behavior Scale Version 2 (VABS II), and Pediatric Quality of Life Inventory (PEDS-QL). Vital parameters (i.e., oxygen saturation, SpO2, and Heart Rate, HR) and the scores at the questionnaires assessing stimulation-induced sensations will be also checked to assess the safety and the tolerability of the stimulation. Lastly, the feasibility and the acceptability of the training will be assessed by considering, respectively, the number of patients completing the training/the number of sessions for each patient and the response to *ad-hoc* questionnaires for the patients and their parents. All primary and secondary outcomes will be collected at each time point, except for the PEDS-QL and VABS II, which will be administered only at T0 and T2. Furthermore, vital cardiovascular parameters and the questionnaires assessing stimulation-induced sensations will be examined during each stimulation session. The acceptability questionnaires will be administered only after the end of the training (T1) (see Figure 1).

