## Patient selection

Male and female children and adolescents with a diagnosis of CP will be considered for eligibility if they are aged from 6 to 17 years. Inclusion criteria will comprise: the presence of clinical signs of unilateral or bilateral upper limb deficits, with a difference at least of 25% between the more affected and the less affected one at Box and Block test; a Magnetic Resonance Imaging confirmed diagnosis according to Surveillance of Cerebral Palsy (SCPE) criteria (37); MACS level I, II, III; Gross Motor Function Classification System level (GMFCS) I, II, III; Visual Function Classification System level (VFCS) between I, II, III; and IQ > 50. The exclusion criteria will include the presence of cochlear implant, cardiac pacemaker, ventriculoperitoneal shunt, neuro-stimulators, clips, fragments or metal splinters in the brain or skull except for titanium; treatments for spasticity or functional surgery of the upper limb in the previous 6 months or planned during the duration of the study, and uncontrolled epileptic seizures in the last 2 years. Before being included in the study, physicians will ensure thorough comprehension of the study’s purpose and design. The parents of the participants and each participant itself have to indicate their willingness to participate before being included.

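### The stratified randomisation cannot be carried out as written: MACS II sits in both severity classes, IQ 71 in neither IQ class, and a randomised pair may straddle classes

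*Protocol article*

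**What the plan says.** All the rules are in the Design section of the protocol article.

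- **Severity:** MACS level, "classified as low to middle (I-II level) or as middle to high (II-III"). Patient selection admits "MACS level I, II, III".
- **IQ:** "low IQ value (from 50 to 70) and high IQ value (> 71) will be distinguished". Patient selection requires an IQ above 50.
- **Age:** "children (from 6 to 11 years old patients) and adolescents (12–17 years old patients"). These two classes are disjoint and complete.
- **Pairing:** children are matched on severity, IQ or age "by meeting at least two out of these three criteria".
- **Unit of allocation:** "Each pair will be randomly assigned to the active or to the sham tVNS group".
- **Stratification:** "The randomization will be stratified based on IQ, MACS level, or age", followed at once by "As for the matching within each pair, at least two out of these three criteria must be encountered".

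The same section gives 1:1 computer-generated blocked allocation, run by independent staff. Statistical analysis plans group-by-time ANOVAs, with t-tests and chi-square tests for baseline differences. It names no covariate.

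**The concern.** A stratification factor must give each randomised unit exactly one value. Three of the stated rules prevent this.

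1. One of the three eligible MACS levels has two severity classes.
2. One eligible IQ score has no class. (The low class also starts at 50, which is not eligible; that has no effect.)
3. The unit is the pair, but the matching rule allows its members to lie in different classes of one factor.

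The *or* in the stratification sentence then leaves open which factors are used at all.

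At stake is the balance that stratification is meant to give. The article itself treats these characteristics as relevant to response: the Introduction says that children under 8 were more likely to improve, and the Discussion expects response to vary with age and clinical impairment. With 11 pairs per arm, chance imbalance is a real possibility. The baseline tests can detect an imbalance but do not correct it, and the planned model does not adjust for it.

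**Working it through.** **Plan's own figure.** The plan has 22 children per group, f(U) = 0.35, three time points and alpha 0.05. Taken as the plan takes it, lambda = 0.35² × (44 − 2) × (3 − 1) = 0.1225 × 84 = 10.29 on 2 and 84 df, and power is 0.812 (0.791 at N = 42). The stated 0.80 is reproduced, and this point does not change it. The 44 children form 22 pairs, 11 per arm.

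**Count of admissible pair types.** Leave out IQ 71. There are 3 MACS × 2 IQ × 2 age = 12 child profiles, of which 4 (all MACS II) have two severity classes. Read the MACS overlap generously, at pair level: I–II and II–III pairs match and take the class that they share, and only I–III fails.

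- Match on all three: 4 IQ-by-age cells × 5 MACS combinations (I–I, I–II, II–II, II–III, III–III) = 20.
- Differ on severity only: I–III in each of 4 cells = 4.
- Differ on IQ only: 2 age classes × (9 − 2) MACS combinations = 14.
- Differ on age only: 2 IQ classes × 7 = 14.
- Total: 20 + 4 + 14 + 14 = 52 unordered types.

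The number of types with exactly one stratum depends on how the *or* is read:

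| Factors that stratify | One stratum | No single stratum |
|---|---|---|
| MACS, IQ and age | 16 | 36 (32 straddle a factor, 4 are fully matched II–II) |
| MACS only | 40 | 12 (4 I–III, 8 II–II) |
| IQ only | 38 | 14 |
| Age only | 38 | 14 |

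No reading removes the problem. These are types, not frequencies.

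**Expected number among 22 pairs.** The document gives neither the patient mix nor the pairing practice. The assumptions are MACS I/II/III of 33/33/33, 25/50/25 or 40/20/40 per cent, low IQ in 20–35% (up to 50% in the random-pairing row), age split 50:50, and all three factors stratifying. All but the optimised rows also put 2% of children at IQ 71.

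| Pairing practice | Pairs without a single stratum |
|---|---|
| All children available at once, optimised, one pool | about 1–3 of 22 |
| Same, within three sites (16, 14 and 14 children) | about 4–6 of 22 |
| First admissible partner in order of arrival | about 15–17 of 22 |
| Random admissible pairs | 69–78% |

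The IQ 71 gap alone touches about 2–3% of pairs.

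**Chance imbalance if stratification does not work.** With 11 pairs per arm and a pair-level characteristic present in K of 22 pairs (K assumed), the hypergeometric distribution gives:

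- K = 11: a split of 8:3 or worse has probability 2 × (1 + 121 + 3,025 + 27,225) / 705,432 = 0.086.
- K = 8: a split of 6:2 or worse has probability 2 × (364 + 8,008 + 56,056) / 705,432 = 0.183.

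**The case against.** The strongest reply is that the MACS overlap is deliberate. The classes come directly after the sentence on pairing, and as a matching rule they make sense: adjacent levels may be paired, I with III may not. That reading is plausible, and the count above adopts it. It narrows the problem but does not remove it, because II–II pairs still fit both classes and the same classes are named for stratification.

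A second reply is that a journal article may leave the handling of discordant pairs and the block size to the full protocol. That is fair, and the absence of those details is not the point. The point is that the stated classes and the stated unit of allocation do not fit together.

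A third reply is that the IQ gap is one score and probably a slip. That stands.

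Some stronger inferences are tempting, and the document does not support them:

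- **Most pairs have no stratum.** This holds only if pairs are formed at the minimum rule; optimised pairing brings it down to a few.
- **The strata are too sparse to work.** A full 2 × 2 × 2 crossing is not stated, centre is not named as a factor, and no block size is given. Even with 8 equally likely strata and blocks of two pairs, the chance of an odd count in a stratum is (1 − 0.75²²)/2 ≈ 0.50. That gives about 4 unfilled blocks against (22 − 4)/2 = 9 full ones, so most blocks would be complete.
- **Staff choose the stratum at enrolment.** This is conjecture, since independent personnel run the allocation.

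**Conclusion.** The concern holds in limited form. As written, the stratification cannot be executed for every eligible pair, whichever factors the *or* selects. Straddling pairs are the main cause under three-factor stratification, the MACS II overlap comes second, and IQ 71 is minor. The share of real pairs affected is unknown, from about 1–6 to about 15–17 of 22, and the range rests entirely on assumed mixes and pairing practice.

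A reader might infer that the treatment comparison is biased. It is not: allocation remains random, and blocked 1:1 allocation still aims at equal numbers of pairs per arm. The loss is in assured balance on severity, IQ and age, which the unadjusted ANOVA does not make good. Nor do the loose classes prevent adjustment, because actual MACS level, age and IQ must be known to establish eligibility.

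**What to change.** **Randomisation.**
- For stratification, use classes that are disjoint and complete, for example MACS I versus II–III (or the actual level), IQ 51–70 versus 71 and above, and age 6–11 versus 12–17. The adjacent-level rule for MACS can stay as a matching rule if it is labelled as such.
- Name the few factors that actually stratify, and replace the *or*.
- Define each pair's stratum by a fixed rule that also covers discordant pairs, for example the higher MACS level of the two children, or the age class of the younger.

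Requiring pairs to agree on MACS class, or changing to minimisation, is optional. Each is a trade-off and is not needed to correct the text.

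**Analysis.** Adjust for each child's actual MACS level, age and IQ, including pairs already randomised. Include the interactions of these covariates with time, because main effects alone leave the group-by-time test essentially unchanged.

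**Cost.** A short amendment, a new allocation list for the remaining pairs, and a few degrees of freedom. With MACS as three levels, the covariates use 2 + 1 + 1 = 4 of 42 between-child error df, or 8 of 84 for the interaction. Neither the sample size nor the treatment changes.

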**Figure 1 fig1:**
[figure not shown]
Flow chart of patient’s inclusion and experimental procedures. ^*^The PedsQL and VABS-II will be administered only at T0 and T2, while all other measures will be administered at all timepoints.

Each pair of patients will be randomly assigned to one of two groups (active vs. sham group) with an allocation ratio 1:1, through a computer-generated blocked randomization procedure conducted by independent personnel not directly involved in performing the intensive training. The patients and their parents, the personnel responsible for conducting the bimanual training and analyzing clinical data will be kept blind to the group allocation. Instead, the coordinator of the study and the personnel administering the tVNS will be “not blind.” With respect to the clinical assessment, the staff administering and scoring the scales will be blinded to group allocation. Questionnaire scores and neuropsychological tests will not contain personal information about the patients, who will be identified by an alphanumeric code. All records that contain names or other personal identifiers, such as informed consent forms, will be stored separately from study records identified by code number. In order to uphold the overall quality and credibility of the clinical trial, instances of code breaks should be limited to exceptional circumstances, where knowledge of the actual treatment is deemed absolutely necessary for the ongoing management of the patient. The intensive treatment will take place at the Scientific Institute, IRCCS E. Medea in Bosisio Parini (Lecco, Italy; study sponsor), Fondazione Mondino IRCCS in Pavia (Italy), and ASST Ospedali Civili in Brescia (Italy). The SPIRIT checklist used for protocol reporting can found in the Supplementary material.

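### About 22 pairs are randomised within strata of IQ, MACS level or age but not of centre, although three hospitals deliver the training and the stated ANOVA has no centre term

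*Protocol article*

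**What the plan says.** All places are in the protocol article.

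- **Unit and size (Design).** The trial is described as a "sham-controlled pre-post-test study involving 44 children and adolescents with CP", and "Each pair will be randomly assigned to the active or to the sham tVNS group". Two children per pair make 22 allocations.
- **Method (Design, after Figure 1).** Allocation is 1:1, "through a computer-generated blocked randomization procedure conducted by independent personnel not directly involved in performing the intensive training". No block size is given.
- **Stratification (Design).** "The randomization will be stratified based on IQ, MACS level, or age". Each factor has two classes. MACS is "classified as low to middle (I-II level) or as middle to high (II-III"; for age, "two group levels will be identified for children (from 6 to 11 years old patients) and adolescents (12–17 years old patients"; for IQ, "low IQ value (from 50 to 70) and high IQ value (> 71) will be distinguished".
- **Centres (Design, after Figure 1).** "The intensive treatment will take place at the Scientific Institute" in Bosisio Parini and at two further hospitals, in Pavia and Brescia.
- **Analysis (Statistical analysis).** The repeated-measures ANOVA is described with group (active, sham) and time (T0, T1, T2).
- **Sizing (Sample size calculation).** 22 children per group, power 0.80, alpha 0.05, f(U) = 0.35.

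**The concern.** Both arms receive 30 hours of training that a therapist adapts to each pair. Therapist and site are therefore plausible sources of variation in gain, and the stimulation effect is a difference on top of that gain. If one hospital's pairs fall mostly in one arm and that hospital's children gain more or less than the others, part of the hospital difference appears as a stimulation effect or hides one. Neither the stated allocation nor the stated model guards against this.

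A second, smaller matter is that stratifying few units finely leaves blocks incomplete, so the arms need not come out at the 11 pairs each that the sizing assumes.

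**Working it through.** **1. The plan's own figure.** For the group-by-time test in the G*Power SPSS form, lambda = f² × (N − k) × (m − 1), with k = 2 groups and m = 3 time points.
- N = 44: lambda = 0.1225 × 42 × 2 = 10.29, df 2 and 84, power 0.812.
- N = 42: lambda = 0.1225 × 40 × 2 = 9.80, df 2 and 80, power 0.791.

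The smallest even N that reaches 0.80 is 44, so the stated size is reproduced.

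**2. Power with unequal arms.** Multiply lambda by 4 × n1 × n2 / 44².

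| Children per arm | Pairs | Factor | Power |
|---|---|---|---|
| 22 v 22 | 11:11 | 1.000 | 0.812 |
| 24 v 20 | 12:10 | 0.992 | 0.809 |
| 26 v 18 | 13:9 | 0.967 | 0.798 |
| 28 v 16 | 14:8 | 0.926 | 0.780 |

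**3. How often the arms are unequal.** Crossing all three factors gives 2 × 2 × 2 = 8 cells, and 22 / 8 = 2.75 pairs per cell. Simulated with equal cells and blocks of 2 to 4 (block size assumed):
- 8 cells: not 11:11 in about 60 to 70% of trials; 9:13 or worse in 11 to 25%.
- 4 cells (two factors crossed): not 11:11 in 45 to 57%.
- Simple coin tossing: 9:13 or worse in 52% (binomial).
- One unstratified list in blocks of 2: always 11:11.

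**4. Arm by centre.** Centre sizes are not stated. Share of trials in which at least one centre has 4 or more extra pairs in one arm:
- sizes 10/6/6, any 11:11 allocation that ignores centre: 34%;
- sizes 10/6/6, blocks within the 8 patient cells: about 41 to 47%;
- sizes left to chance, with equal or 50/25/25 expected shares and the same cells: 29 to 35%.

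**5. What such a split could do.** Under a sustained effect at T1 and T2 and compound symmetry, lambda = 11 × (2/3) × 2 × d², where d is the effect in SDs of change. So d = √(10.29 / 14.67) = 0.84.

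Assume that a 6-pair centre differs in mean gain by 0.5 SD of change. A 5:1 split there, with 11 pairs per arm, shifts the arm difference by 0.5 × (5/11 − 1/11) = 0.18 SD, or 0.18 / 0.84 = 22% of the sized effect.

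How typical is that? The chance that a given 6-pair centre splits 5:1 or worse is 2 × [C(11,6) + 11 × C(11,5)] / C(22,6) = 2 × 5,544 / 74,613 = 15%. The number of its pairs in the active arm has variance 6 × 0.25 × 16/21 = 1.14, so the shift has mean zero and SD √1.14 / 11 = 0.10.

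**6. The remedies (sizes 10/6/6 unless noted).**
- Minimisation over centre and the three factors: a within-centre gap of 4 or more pairs in about 13%, and 9:13 or worse in about 3%. A rerun with the favoured arm chosen with probability 0.8 gave 15% and 5%; with 0.9 it gave 7% and 1%.
- Centre-only strata: no within-centre gap of 4 or more. With sizes left to chance as in step 4, splits of 9:13 or worse occur in 0 to 4%.
- Centre plus one patient factor (6 cells): arms unequal in about 51 to 64%, so equal arms are not restored.

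**The case against.** The other side has a good deal.

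- **Unequal arms barely matter.** A reader might infer that fine stratification leaves the trial underpowered. It does not: a 9:13 split still gives 0.798. Nor is the allocation as loose as a coin toss (11 to 25% against 52% for 9:13 or worse). This stands.
- **The 8 cells are one reading.** The text joins the factors with *or* and adds a two-of-three rule, MACS II lies in both classes, and a pair that differs on one factor has no single cell. This stands, so the cell figures are conditional. The centre point does not depend on them: ignoring centre in a perfectly balanced 11:11 list still gives 34%.
- **The harm is chance, not bias.** A reader might infer that the treatment estimate is biased. Randomisation remains valid, and the shift averages zero with SD about 0.10 even under the assumed 0.5 SD centre difference. The 0.18 SD case is in the tail. Stable differences in level between centres cancel in the pre-post comparison; only differences in gain count. The HABIT-ILE section relies on trained therapists for consistency, and therapists and assessors are blinded. All this limits the size of the problem without removing it.
- **Patient factors are a defensible choice.** The Introduction gives a prognostic reason for age and none for centre. That supports keeping age, but not leaving centre out of both the allocation and the model.
- **An article condenses the full plan.** A full protocol or SAP could add detail, such as block size or further model terms. But the article does list its stratification factors, and centre is not among them.

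**Conclusion.** The point holds as a moderate weakness of design. The named stratification factors omit centre, and the analysis as described does not compensate. With only 22 allocations over three hospitals, a marked arm-by-centre imbalance is common: roughly 35 to 45% at assumed sizes of 10/6/6, and 29 to 47% over all the assumptions tried. What it costs is precision and credibility, and only if gain differs by centre, which the article neither states nor rules out. The possible incomplete blocking is secondary and has negligible effect on power.

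The conclusion rests on assumed centre sizes and block sizes. The size of any shift rests further on an assumed 0.5 SD difference in gain.

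**What to change.** **Allocation.** For pairs still to be randomised, use minimisation with a random element over centre, age, MACS and IQ. The classes must first be made non-overlapping and exhaustive (MACS II is in two, an IQ of 71 in none), with a rule for pairs whose members differ on a factor. The simpler alternative is to stratify by centre alone with small, randomly varied blocks. Varied sizes matter because the coordinator and the staff giving the stimulation know the allocation and could predict the end of a fixed block. Do not add centre to the existing factors: 3 × 8 = 24 cells for 22 pairs would undo the blocking further, with 9:13 or worse in 35 to 44% of trials.

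**Analysis.** Include centre and the balancing factors in the model, crossed with time, because a plain centre effect removes only differences in level. Centre (2 df) and three binary factors (3 df), each over 2 time contrasts, use 10 of the 84 error df. This step helps even if allocation is already complete.

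**Cost.** Under the Ethics statement, an important modification is reported to the funder and the registry and approved by the Ethics Committees. The allocation scheme changes mid-trial and must be reported as such. With centre-only strata, the patient factors are balanced less tightly by design and rely more on adjustment.
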